### The intervention

SAFE is a manualised intensive programme of systemic family therapy designed to treat maladaptive autistic symptoms and mental health-related difficulties encountered by families of children with autism. SAFE provides an array of therapeutic activities based on attachment theory, established systemic practice and the known visual processing preferences of people with autism.^59–61^ SAFE is best seen as a toolkit with a variety of activities which can be applied to family therapy flexibly. For example, a very young child will engage with activities in a different way to teenagers. Activities include visual tasks, drawing, modelling, role-play and tracking circular patterns. Sessions are led by family need and the therapists and family work collaboratively, often in a playful way, using family resources, therapist expertise and the tools that SAFE provides. SAFE draws heavily from well-documented active and playful approaches in family therapy practice and literature.^62^

Each therapy session will include two therapists with a minimum of intermediate family therapy level of qualification and 4 days training in SAFE principles. Prior to the therapy sessions parents allocated to SAFE will complete an adapted version of the parent development interview,^60^ which will provide therapists with background information on family experience. The reflective functioning questions of this interview will also be revisited as an opportunity to discuss change at the 24-week follow-up. Between weeks 1 and 16, families allocated to the SAFE intervention will attend five 3-hour SAFE therapy sessions. Sessions 1 and 5 are multifamily sessions and will take place in a community setting. Sessions 2, 3 and 4 are for individual families and will take place in a community venue or the family home. The therapists will facilitate sessions which will be video recorded, as is usual practice for therapy sessions. The videotapes will be used by the therapists in supervision sessions and preparation for subsequent sessions.

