Following completion of the therapy programme, families will attend a group follow-up session at 24 weeks post-allocation. Families will discuss any changes they have encountered focusing on their ability to be reflective about challenges faced and solutions tried. Trained support workers from local voluntary groups will attend this follow-up session and will be invited to give the families information about continued support for families of children with autism through existing networks.

Each session will include the following assessments for families to complete:Client Satisfaction Questionnaire 8.The Helpful Aspects of Therapy Questionnaire.A Between-Session Activity (BSA) homework activity. Families will be encouraged to complete a pro forma with key elements of the intervention as prompts for families to track strengths and difficulties in response to SAFE ideas. Completion of the BSA will be recorded.

At the end of each session, the therapists will also complete a training checklist and questionnaire to monitor protocol adherence.

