## Ethics and dissemination

### Risks and safety

Families of children with autism are a potentially vulnerable group. The risks associated with participating in this study are however, considered minimal, with no adverse events anticipated in any participant. For those in the intervention group, there is a slight chance that the SAFE family therapy sessions could lead to an initial increase in family disagreements as family members learn how to change the way they solve problems and talk with one another. However, the purpose of the intervention is ultimately to equip families with skills to handle these difficulties by learning how to change the way they solve problems and improve their communication, and the SAFE family therapists will be available to provide support and will be trained to handle any emerging problems. Should any issues arise the SAFE family therapists will have access to two consultant clinical psychologists to provide further support and advice.

During the trial, the children with autism will remain in the care of the Child Development Centre or the ASDAT and will have access to usual care should any unforeseen circumstances arise. Other members of the family will also continue to be able to seek care and advice from the GP or any other specialist services they are concurrently involved with.

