### Monitoring adverse events

The research team have mechanisms in place to report serious adverse events (SAE) related to mental health. SAEs related to mental health may be volunteered by the participant or discovered by the therapists, research assistants or other member of the research team during the SAFE family therapy sessions, or as a result of direct reporting (e.g. by telephone) by a family member, independent clinician or other informant. SAEs will be recorded from the time of consent until the date the participant completes the follow-up or withdraws from the study.

If the CI considers that the SAE is not, or is unlikely to be, associated with the trial, the CTU will obtain a second assessment of causality from an independent assessor. Any SAE which in the opinion of either adjudicator is possibly related to the trial will be reported to the Research Ethics Committee (REC) within 15 days of the local research team having become aware of the event. All SAEs will be followed until either stabilised if chronic conditions, or resolved.

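### The only serious adverse event route that rests on scheduled staff contact is the SAFE therapy session, so descriptive SAE counts are liable to under-record events in the SUE arm

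*Protocol article*

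**What the plan says.** Under Monitoring adverse events, the protocol article describes how SAEs related to mental health come to light. Participants can come forward themselves. Staff can also find an event, which the article words as "discovered by the therapists, research assistants or other member of the research team during the SAFE family therapy sessions". The third route is a report that reaches the team "as a result of direct reporting (e.g. by telephone) by a family member, independent clinician or other informant". The recording window is the same in both arms: "SAEs will be recorded from the time of consent until the date the participant completes the follow-up or withdraws from the study".

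The contact schedule differs by arm. Under The intervention, between weeks 1 and 16 "families allocated to the SAFE intervention will attend five 3-hour SAFE therapy sessions", and after that "families will attend a group follow-up session at 24 weeks post-allocation". There is also an interview: "Prior to the therapy sessions parents allocated to SAFE will complete an adapted version of the parent development interview". Under Study design, both arms complete outcome measures face to face at baseline and at 32 weeks, with blinded assessors. The paediatric appointment described under Support as usually employed is usual care, not a trial contact.

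On expected harm, Risks and safety describes the risk as minimal, "with no adverse events anticipated in any participant", and then says of the intervention arm that "there is a slight chance that the SAFE family therapy sessions could lead to an initial increase in family disagreements". The section on informing potential participants also tells families that sessions may bring up difficult emotions and lead to disagreement.

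**The concern.** An SAE count by arm can be read only if an event of the same kind has a similar chance of being found in each arm. Here one route exists only for families allocated to SAFE, and it is the only one in which staff meet families on a schedule. The routes open to SUE families depend on someone choosing to report.

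If true rates were equal, SAFE would tend to show more recorded events. If SAFE really caused more events, the excess could be put down to closer observation. The study would have no data to separate the two. This matters even in a small feasibility study, because its purpose is to try out procedures, including data collection, before a definitive trial.

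A second, smaller point is that the event system covers only SAEs related to mental health. The foreseen harm, an early rise in family disagreement, would enter it only if it became such an SAE.

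**Working it through.** The plan states no SAE rate or detection figure, so there is no figure to reproduce. The check is a count of contacts, followed by an illustration on stated assumptions.

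**1. SAE routes by arm (Monitoring adverse events)**

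| Route | SAFE + SUE | SUE alone |
|---|---|---|
| Volunteered by participant | yes | yes |
| Direct report by family member, clinician or other informant | yes | yes |
| Found by staff during SAFE sessions | yes | no |
| Enquiry at the 32-week visit | not named | not named |

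**2. Scheduled trial contacts after allocation and before the 32-week visit (The intervention; Study design)**

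- SAFE: 5 therapy sessions + 1 group session at 24 weeks = 6. Adding the parent interview gives 7. Counting only the therapy sessions proper gives 5.
- SUE: 0.
- Both arms then have the 32-week visit.

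The contrast is 6 v 0, or 5 to 7 v 0 depending on what counts as a session.

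**3. Illustration of the possible size (assumptions, not figures from the document)**

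Let the true SAE risk *p* be equal in both arms. Let *s* be the chance that an event is found by the passive routes, the same in both arms. Let *c* be the independent chance that a SAFE session finds it.

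- Detection in SUE: *s*
- Detection in SAFE: 1 − (1 − *s*)(1 − *c*)
- Apparent risk ratio: [1 − (1 − *s*)(1 − *c*)] / *s*

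| *s* | *c* | Detection in SAFE | Apparent ratio |
|---|---|---|---|
| 0.8 | 0.3 | 1 − 0.2 × 0.7 = 0.86 | 0.86 / 0.8 = 1.075 |
| 0.5 | 0.5 | 1 − 0.5 × 0.5 = 0.75 | 0.75 / 0.5 = 1.50 |
| 0.3 | 0.8 | 1 − 0.7 × 0.2 = 0.86 | 0.86 / 0.3 = 2.87 |

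The ratio exceeds 1 whenever *c* > 0 and *s* < 1. So the direction follows from the routes, while the size depends wholly on the assumed values.

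**4. Scale in this study**

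36 families at 2:1 gives 24 and 12. With *p* = 0.10 and *s* = *c* = 0.5, expected recorded events are 24 × 0.10 × 0.75 = 1.80 in SAFE and 12 × 0.10 × 0.5 = 0.60 in SUE, or 7.5% v 5.0% of families, although the true risks are equal. Counts this small would not show such a difference reliably. The point therefore concerns the procedure, not a result this study could establish.

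**5. Where the foreseen harm can appear**

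- The topic guide for the family focus groups includes potential harm of the intervention (Outcome measures).
- SCORE-15, PHQ-9 and GAD-7 are collected in both arms at baseline and 32 weeks.
- The focus groups are optional and come after the 32-week assessments. A score at 32 weeks may miss a rise that occurred during weeks 1 to 16 and then settled.

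**The case against.** The strongest case against the point has five parts.

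- **No harms comparison is planned.** Data analysis limits contrasts between groups to one confidence interval for the primary outcome, and SAE reports serve causality assessment and reporting to the ethics committee. This stands. A reader might infer that the plan will produce a biased harms estimate, but it plans no such estimate. What remains is that any descriptive listing by arm will be hard to read.
- **The foreseen harm is covered.** A reader might infer that it goes unmeasured. The document does not support that: the qualitative work asks about harm, and family functioning, depression and anxiety are scored in both arms. Only the narrower point stands, that an early and transient rise is not recorded as an event.
- **SUE families are not out of sight.** Passive reports are open to them, they attend at 32 weeks, and the resource-use questionnaire covers the child's hospital days with no restriction by arm. So detection in SUE is liable to be lower, not absent.
- **The wording may be looser than it looks.** The routes are introduced permissively, and the reference to SAFE sessions might qualify only some of the staff listed. But no other occasion for discovery by staff is given.
- **An article condenses.** The full protocol may prompt for SAEs at the 32-week visit. If so, one sentence settles the matter. The point rests on the routes that the article does state, which depend on allocation.

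That the main trial would inherit these procedures is a reasonable worry, but the document does not say so.

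**Conclusion.** The point holds in a limited form. As described, the only SAE route resting on scheduled staff contact is closed to SUE families: six scheduled contacts v none before the 32-week visit, over the same recording window. Descriptive SAE counts by arm are liable to under-record SUE events relative to SAFE events.

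The size cannot be derived from the document. The illustrative ratios of 1.075 to 2.87 rest on assumed detection probabilities of 0.3 to 0.8 and equal true risk, and should not be cited as an estimate of bias. It would go too far to say that the harms data are biased, that SUE events are missed altogether, or that the foreseen harm is unmeasured.

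The change is worth making because it is cheap and the study exists to test procedures. It does not affect the validity of the planned primary outcome interval.

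**What to change.** 1. At the existing 32-week visit, ask both arms the same short, neutrally worded questions about mental-health SAEs and about marked family conflict or distress since allocation. Ask them after the outcome measures are complete, to protect assessor blinding. If the full protocol already does this, say so under Monitoring adverse events.
2. Record the source of every report (session, visit, volunteered, informant), allowing more than one. An event already known from a session should still count as visit-elicited if the family reports it at the visit; otherwise the visit list would fall short in the SAFE arm.
3. List visit-elicited and session-detected events separately and descriptively by arm. No formal comparison is needed. With the same enquiry at the same time, and similar recall, equal true risks would give an expected ratio of 1 for visit-elicited events.
4. Reconcile the statement in Risks and safety that no adverse events are expected with the harm named in that section and in the participant information.

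**Cost.** A few questions at a visit both arms already attend, one case report form field, a minor amendment and slightly more recorded events. There is a small risk that answers reveal allocation to the assessor, limited by asking last. Families who withdraw before 32 weeks will still be covered only by the other routes.

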### Dissemination

If the feasibility study meets progression criteria an important part of our dissemination plan is to raise awareness of the need for a larger multicentre trial. We will, therefore, offer targeted summaries of our findings and presentations to policy makers. The findings will also be broadly disseminated, but in a manner appropriate to a feasibility study. We plan national conference presentations and published papers to inform clinicians, academics and therapists about the possible benefits of SAFE and generate interest in the future trial. We will make use of our existing connections including the Association for Family Therapy, the National Autistic Society and the Institute of Family Therapy to reach relevant audiences. Our qualitative findings will also be published with detailed accounts of the families’ reactions to SAFE and their views on its effectiveness. We will also provide forums for participating families to share their own experiences of the intervention with wider audiences through existing networks, groups and events across the UK.

Our Family Consultation Group will be integral to our dissemination plan. Their involvement will include presenting their experiences as delegates at national and international conferences, being active co-authors on published papers, leading the organising committee for a local event sharing findings with families, key local stakeholders, clinicians and other interested partners; and liaising with other bodies to raise awareness of the study findings including Autistica, The National Autistic Society and the Brandon Trust.

### Informing potential participants of possible benefits and known risks

The participant information sheets and leaflets will provide potential participants with information about the possible benefits and risks of taking part in the trial. For example, the participants will be informed that a potential risk of receiving the SAFE therapy is that the sessions may evoke difficult emotions and feelings; this could lead to family disagreement as they move towards change. The families will also be informed that benefits of the trial include the possibility of improved coping skills when faced with challenges and contribution to finding out if SAFE can progress to a national trial. Participants will be given the opportunity to discuss risks and benefits with a member of the research team prior to consenting to participate.

### Obtaining informed consent from participants

All participants will receive a leaflet and information sheet prior to consent. There are two versions of the information sheet, one for adults and one for children. In the leaflet, parents are encouraged to explain the trial to their younger children and some guidance for doing this is provided. The information sheet states that the participants have the right to withdraw at any point during the trial and that data collected from them will be confidential. All participants will have a home-visit prior to consent from a member of the research team and will be able to ask questions or go through the information verbally. Participants will have the process of the study explained to them including the estimated time they will have to wait prior to randomisation and starting the intervention if allocated to that arm.

### Data protection/confidentiality

Participants will be given a unique identification number. The data will be pseudo-anonymised in the sense that there will be an identification number on the documentation but otherwise no means of identifying the individual to which the data relates. The research team will ensure that participants’ pseudo-anonymity is maintained on all documents. Data will be collected and stored in accordance with the current legal and regulatory documentation. Electronic study records will be stored in a SQL server database, stored on a restricted access, secure server maintained by Plymouth University. Data will be entered into the database via a bespoke web-based data entry system encrypted using secure sockets layer (SSL). Access to electronic data will be permission based, and at the discretion of the clinical trials unit data management team.

Anonymised paper-based study data will be stored in locked filing cabinets. Copies of study data retained at the lead study site will be securely stored for the duration of the study prior to archiving. Video data will be transported via encrypted memory sticks and will be transferred to a password-protected computer. The clinical trials unit data team will have access to study data, including identifiable data. Other members of the study team and the trials unit will have restricted access to pseudo-anonymised study data. Access will be granted to the sponsor and host institution on request, to permit study-related monitoring, audits and inspections.

### Research governance and the conduct of the trial

The trial will be conducted to protect the human rights and dignity of the participant as reflected in the Declaration of Helsinki. An important factor in protecting the participants is ongoing consultation with the SAFE Family Consultation Group. A representative of this group is a member of the research team and is involved in decision-making processes. The research team including the family consultation group are proactive in minimising discomfort and risk for participants, respecting their wishes over science and society, respecting the right to withdraw and the need for families to have access to all relevant information.

The Chief Investigator will be responsible for the overall conduct of the study, keeping it to schedule and within budget. Working closely with the CTU, she will be the focal contact for enquiries from both sites. The CTU will manage the study, liaise with sites, monitor recruitment, work with the sponsor and report to TMG meetings. The TMG will meet regularly throughout the feasibility study. A Trial Steering Committee (TSC) will have an overarching monitoring responsibility. The TSC is expected to meet three times during the study, but will be additionally convened at the chairman or Chief Investigator’s request.

### Dissemination plans

If the feasibility study demonstrates successful recruitment, data collection and an ability to deliver the intervention, an important part of the dissemination plan is to raise awareness of the need for a larger multicentre trial. Targeted summaries of the findings and presentations will be disseminated to policy makers. The findings will also be broadly disseminated, but in a manner appropriate to a feasibility study. National conference presentations and published papers will be prepared to inform clinicians, academics and therapists about our feasibility results and generate interest in the future trial. Existing connections including the Association for Family Therapy, the National Autistic Society and the Institute of Family Therapy will be used to reach relevant audiences. The qualitative findings will also be published with detailed accounts of the families’ reactions to SAFE and their views on its usefulness. A summary of study results in plain English will be available on the Peninsula Clinical Trials website.

### Clinical trials authorisation and ethical approval

Clinical trials authorisation is not required. The trial will be conducted in accordance with the protocol, the principles of the Declaration of Helsinki and International Conference of Harmonisation - Good Clinical Practice (ICH GCP). Any amendments of the protocol will be submitted to the sponsor, Health Research Authority and REC for approval.

### Trial sponsorship

The trial is sponsored by PHNT.

### Trial Steering Committee

The TSC will include an independent chair and two other independent members, along with the lead investigator and the other study collaborators including a parent representative. They will meet once a year.
